
### Phone Coaching

A coaching protocol was developed based on the Efficiency Model of behavioral intervention technology support [16] and supportive accountability [17]. A similar coaching protocol has been implemented in a prior study of the IntelliCare apps [18]. The primary aims of coaching are to address usability issues, increase engagement with the apps, promote fit by assessing participants’ needs, promote knowledge acquisition of the skills found in the apps, and encourage implementation of the skills in participants’ lives. In keeping with the prior study of IntelliCare [18], coaches are instructed to focus on app-related issues and to refrain from doing more traditional counseling with participants. An initial 30-min coaching call will focus on orienting participants to downloading and using the apps, setting expectations of the coach’s role, assessing how the apps may meet participants’ needs, and building rapport. Participants will also be told that they can contact coaches at any time with any app-related questions. Participants who contact coaches for crisis management will be connected with a nearby mental health service provider. Any participant inquiries will receive a response within 1 working day. Following the initial coaching call, participants will receive a short message service (SMS) text message (via Qualtrics Survey Platform SMS tool) every week to remind them to download and try 1 to 2 new IntelliCare apps. Coaches have a bachelor’s degree (not in counseling) and are trained and monitored by the lead author (PC), who has a PhD in clinical and community psychology and over 8 years of experience in conducting psychological assessments and psychotherapy. Coaches received a detailed coaching manual and will attend weekly supervision meetings throughout the duration of the study.

To encourage engagement with the apps, coaches will refrain from making explicit recommendations regarding which apps to use and how often to use them. Instead, following prior work [18], coaches will instruct participants to review the apps, remind them of their needs and goals, and ultimately allow participants to make their own decisions regarding which apps to use. If participants are resistant to making their own decision regarding which apps to use, coaches will be permitted to give recommendations. Precautions were made to help ensure that coaching calls focus on the IntelliCare apps. Specifically, coaches are provided a detailed and scripted coaching manual that they are told to follow closely. Coaches received weekly training and engaged in role playing exercises with the lead author (PC) on how to conduct coaching calls. Finally, a 10-min phone call 3 weeks after the initial coaching call will serve as a check-in to make sure that participants have a clear understanding of the app program and to answer any lingering questions. All described components of this study have been approved by the University of Virginia institutional review board for Health Sciences Research.

### Measures and Outcomes

#### Primary Objective and Measures

Because a significant barrier to conducting this study is the enrollment of participants in a busy clinical setting, we will consider the study feasible if (1) we are able to recruit 1 to 2 participants per week from a single clinic over 29 weeks; (2) complete follow-up in at least 50% of all recruited subjects; and (3) observe a median app launch rate of around 3.0, as found in prior work [18]. Participants will be asked to provide feedback on the apps and coaching at the end of the study period. The Usability, Satisfaction, and Ease of use (USE [28]) short form scale will be used to examine usability of the IntelliCare apps. It is composed of items that assess user experience (eg, “I would recommend it to a friend,” “It is easy to learn to use it,” and “It is simply to use”). Items are scored on a 7-point Likert scale (1=strong disagree and 7=strongly agree). The USE measure is a validated scale that is commonly used to evaluate user experience of digital interventions. Participants will be asked to describe the most positive and negative aspects of the apps and which apps were most and least helpful and why. If participants stopped using the apps, they will be asked to comment on why and barriers to using the apps.

Participants will also be asked to provide open-ended feedback. Research staff will conduct telephone interviews with participants, which will cover the following topics related to using the apps: general impressions, design quality, technical needs, and design suggestions to promote app implementation and usage. In addition, participants will be asked to provide feedback on the following aspects of phone coaching: general experience with coaches, usefulness of coaching, additional or unmet coaching needs, and suggestions to improve the coaching experience. Thematic analysis will be used to analyze qualitative data gathered from interviews. Data yielded from this mixed-methods approach will be used to make improvements to the apps and phone coaching in future work.

#### Secondary Objectives and Measures

Several measures will be administered at baseline and after 7 weeks. Demographic and background variables (eg, age, gender, and race or ethnicity) will be collected at the baseline session. Disease variables (eg, cancer site, stage, and treatments) will also be collected from the patient’s electronic medical records. Measures will be administered and completed via a secure data collection website (Qualtrics Survey Platform). Data are stored in a secure database that is only accessible to study personnel to ensure confidentiality.

Depression symptoms will be assessed with the 4-item scale from the Patient-Report Outcomes Measurement Information System [29] 29-item profile version 2.0 (PROMIS-29 Profile v2.0). PROMIS, a US National Institutes of Health Roadmap program, provides sensitive and reliable measures of patient-reported outcomes. A goal of PROMIS is to allow organized and effective assessment of patient-reported outcomes across a range of chronic diseases. Participants are asked to report (1=never and 5=always) the degree to which they experienced various depressed states (eg, “I felt worthless” and “I felt hopeless”) over the past 7 days. Continuous anxiety symptoms will be assessed with the 4-item scale from the PROMIS-29 Profile v2.0. Participants are asked to report (1=never and 5=always) how much they have experienced different anxious states (eg, “My worries overwhelmed me” and “I felt fearful”) over the past 7 days.

The Patient Health Questionnaire-4 (PHQ-4; [30]) is widely used in cancer settings as a brief screener of general distress and symptom burden [30] and is well validated in both general and clinical samples [30,31]. The PHQ-4 will be administered to examine whether using mental health apps leads to a clinically significant decrease in general distress and overall symptom burden and will be used to classify individuals based on the severity of their mood symptoms at baseline and postassessment. Individuals are asked to rate (0=not at all and 3=nearly every day) the degree to which they have experienced different states (eg, “Little interest or please in doing things”) over the past 2 weeks. Scores range from 0 to 12. A score of 6 to 8 indicates moderate mood symptoms, whereas a score of 9 and higher indicates severe mood symptoms. Symptoms assessed by the PHQ-4 and PROMIS anxiety and depression subscales (of PROMIS-29) will be used to obtain estimates of the treatment effects and the variances of treatment effects for a larger trial.

Several measures will be administered to both patients and caregivers. Life meaning will be assessed with the 4-item PROMIS [29] Life Meaning/Purpose scale. Participants are asked to report (1=not at all and 5=very much) the degree to which they agree with 4 statements (eg, “My life has meaning” and “I have a clear sense of direction in life”). Sleep quality will be assessed with the 4-item PROMIS [29] Sleep Disturbance scale from the PROMIS-29 Profile v2.0. Participants are asked to report (1=very poor and 5=very good) on their sleep quality over the last 7 days. They are also asked to report (1=not at all and 5=very much) the degree to which they experienced sleep difficulties (eg, “I had difficulty falling asleep”) over the last 7 days. Patients and caregivers will also complete a measure of health care utilization. Patients will be asked whether they visited the emergency department over the past 2 months, whether any of these visits were related to side effects from cancer treatment, whether they missed a scheduled appointment for cancer treatment, and whether they have used cancer support services in the past 2 months. Caregivers will be asked whether they visited the emergency department over the past 2 months, how many times they visited a primary care doctor for anything other than routine care, and whether they have used cancer support services in the past 2 months.

Several additional scales will be administered to patients. Physical functioning will be assessed with the 4-item PROMIS [29] Physical Health scale from the PROMIS-29 Profile v2.0. Participants are asked to report (1=unable to do and 5=without any difficulty) the degree to which they are able to perform 4 activities (eg, “Are you able to go for a walk of at least 15 minutes?” and “Are you able to run errands and shop?”). Engagement in social activities will be assessed with the 4-item PROMIS [29] Ability to Participate in Social Roles and Activities scale from the PROMIS-29 Profile v2.0. Participants are asked to report (1=never and 5=always) the degree to which they agree with 4 statements (eg, “I have trouble doing all of my regular leisure activities with others” and “I have trouble doing all of the family activities that I want to”). Fatigue will be assessed with the 4-item PROMIS [29] Fatigue scale from the PROMIS-29 Profile v2.0. Participants are asked to report (1=not at all and 5=very much) the degree to which they agree with 4 statements and questions (eg, “I feel fatigued” and “How run-down did you feel on average?”) as it pertains to the prior 7 days. Finally, pain interference will be assessed with the 4-item PROMIS [29] Pain Interference scale from the PROMIS-29 Profile v2.0. Participants are asked to respond (1=not at all and 5=very much) to questions assessing pain interference in daily life (eg, “How much did pain interfere with your day to day activities?” and “How much did pain interfere with your household chores?”) as it pertains to the prior 7 days. Finally, participants will respond to a single item assessing pain level over the past 7 days, on a 0 (no pain) to 10 (worst pain imaginable) scale.

Caregivers will be administered the 21-item Caregiver Self-Efficacy scale (CaSES [32]), which was developed to measure self-efficacy in informal cancer caregivers. The CaSES was found to have good validity and reliability in a large sample of caregivers [32]. Items assess caregivers’ perceptions of their duties and capabilities (eg, “I can be positive when I need to be,” “I can continue to provide care when I feel scared,” and “I have the ability to talk openly with the person I care for”) and are scored on a 4-point scale (0=not at all confident and 4=very confident).

Finally, IntelliCare app use data will be collected passively. Specifically, engagement will be ascertained from the number of app launches, defined as a user-initiated event after at least 5 min of no activity [18]. The duration of individual app use sessions will also be used to reflect engagement and is defined as the length between an app launch at the last event in that session.

To understand the preliminary impact of IntelliCare on daily mood, social functioning, and health behavior during the study, patients and caregivers will respond to a short survey every week throughout the study period via the Web. Surveys will be delivered using the Qualtrics Survey Platform SMS tool. Participants will receive an SMS text message on their phone at 8 pm. An embedded link within the SMS text message will automatically connect participants to a secure Qualtrics Survey Platform Web page containing survey items. Weekly surveys are each expected to take 1 to 2 min to complete.

All participants will be asked to report (1=very negative and 5=very positive) how they have felt over the past week and how they expect to feel the following week. They will also be asked about the following behaviors or activities over the past week: how well they have managed negative feelings, how much they have used alcohol or tobacco to cope with negative feelings, amount of physical pain experienced, how connected they felt to family and friends, how much support they received from loved ones, how much support they were able to provide to loved ones, how much anxiety they experienced, how much interest or pleasure they had in doing things, and amount of physical activity. At the end of the survey, participants are reminded to focus on trying out new IntelliCare apps for the upcoming week. They will be asked to note which specific apps they intend to use during the upcoming week.

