**Methods:**

The IntelliCare mental health apps are grounded in evidence-based research in psychology. They have not been examined in cancer populations. This pilot study will adopt a within-subject, pre-post study design to inform a potential phase III randomized controlled trial. A target sample of 50 individuals (with roughly equal numbers of patients and caregivers) at least 18 years of age and fluent in English will be recruited at a US National Cancer Institute designated clinical cancer center. Consent will be obtained in writing and a mobile phone will be provided if needed. Self-report surveys assessing mental health outcomes will be administered at a baseline session and after a 7-week intervention. Before using the apps, participants will receive a 30-min coaching call to explain their purpose and function. A 10-min coaching call 3 weeks later will check on user progress and address questions or barriers to use. Self-report and semistructured interviews with participants at the end of the study period will focus on user experience and suggestions for improving the apps and coaching in future studies.

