### Recruitment Procedure

Breast cancer patients and their caregivers will be recruited from a breast care clinic. Surgical oncologists will help to identify potential participants, who will be introduced to the study during a normal scheduled visit. Surgical oncologists will offer a study flyer to breast cancer patients and their caregivers during a normal scheduled visit. Patients and caregivers who express an interest in learning about the study will then speak to a research staff member, who will provide more details about the study and answer any questions. If an eligible patient or caregiver expresses interest in participating in the study, he or she will be led through the consenting process by a research staff member. Research staff will describe the aims of the study, introduce the IntelliCare apps, and review the study timeline. Infographics will serve as visual aids to improve understanding of the study components and timeline. Individuals who provide written consent will schedule a 30-min coaching call to take place sometime within the next 10 days. They will also be guided to download the apps but will be told not to open them until the coaching call. Downloading the apps at the end of the consenting process will allow coaching calls to be kept to within the allotted 30-min time frame. Participants will also have the option to download a separate app (ie, not part of the IntelliCare app suite) that passively collects location and movement data from their phone’s sensors. This app, Sensus, was developed by University of Virginia researchers [26] and has been used to collect location and movement data in college student samples [27]. Data collected from this app will be used in exploratory analyses to determine whether it is possible to identify behavioral markers of mood and well-being. For example, in a prior study of college students, it was found that the amount of time spent at home was associated with a higher level of anxiety and that more negative affect was linked to a longer homestay duration [27]. Participants will be asked to spend 10 to 15 min to complete measures that assess depression and anxiety symptoms, physical and social functioning, and subjective well-being. Measures will be completed via the Web using Qualtrics Survey Platform through a desktop or laptop computer. Recruitment will cease if the target enrollment is met or funding expires at the end of 2018. The same research staff members are each responsible for consenting participants, conducting coaching calls, and collecting feedback from participants.

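### The 2-month recall for emergency visits and support-service use is longer than the 7-week follow-up, so the follow-up answer takes in time before app use and, on most timings, before baseline

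*Protocol article*

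**What the plan says.** In the Protocol article, Secondary Objectives and Measures, the utilization items for patients read "Patients will be asked whether they visited the emergency department over the past 2 months". For caregivers the text is "Caregivers will be asked whether they visited the emergency department over the past 2 months". Both groups are also asked "whether they have used cancer support services in the past 2 months".

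The same section opens with "Several measures will be administered at baseline and after 7 weeks". The Methods part of the abstract gives the schedule as "Self-report surveys assessing mental health outcomes will be administered at a baseline session and after a 7-week intervention".

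Recruitment Procedure separates consent from first app use: "Individuals who provide written consent will schedule a 30-min coaching call to take place sometime within the next 10 days". On the apps themselves it adds: "They will also be guided to download the apps but will be told not to open them until the coaching call".

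Nothing in the article limits the follow-up recall to the time since baseline or since the coaching call, and nothing mentions an overlap between the two recall windows.

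**The concern.** In a pre-post design the follow-up recall should describe the period under intervention and the baseline recall the period before it. A recall longer than the follow-up interval breaks that separation in two ways.

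- **Time before app use.** Some of what the follow-up answer describes happened before the participant could have opened an app, which dilutes any change.
- **Overlap with the baseline window.** An event in the days shortly before baseline falls inside both windows. The person answers yes at baseline and, truthfully, yes again at follow-up, even with no event since. A real change from yes to no is then hidden.

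The Participants section says that patients in this clinic are mostly early in the diagnostic process, so contact with services just before enrolment is plausible. There is no comparison group that would show or offset the distortion. The article also wants the pilot to rehearse the analyses for a larger trial, so an ill-fitting item could be carried forward.

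**Working it through.** No figure in the article depends on this point, so there is nothing to reproduce first. The check is calendar arithmetic.

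**Inputs**
- W, the recall window: 2 calendar months, which is 59 to 62 days over plausible follow-up dates from April 2018 to February 2019 (average month length gives 60.9 days). From Secondary Objectives and Measures.
- Follow-up interval: 7 weeks = 49 days. From the abstract and Secondary Objectives and Measures.
- L, the lag from baseline to the coaching call: 0 to 10 days, taking baseline as the day of consent. From Recruitment Procedure.
- First app use: not before the coaching call. From Recruitment Procedure.
- The follow-up survey is assumed to be completed on time.

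The article does not settle whether the 7 weeks run from baseline or from the start of the intervention, so both readings are worked.

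**Reading A: follow-up 49 days after baseline**
- Days before baseline = W − 49. From 59 − 49 = 10 to 62 − 49 = 13. Share of window: 10/59 = 17% to 13/62 = 21%. All of these days also lie inside the baseline recall window.
- Days before first app use = W − 49 + L. From 59 − 49 + 0 = 10 to 62 − 49 + 10 = 23. Share: 10/59 = 17% to 23/62 = 37%.

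**Reading B: follow-up 49 days after the coaching call**
- Days before first app use = W − 49 = 10 to 13 (17% to 21%), whatever the lag.
- Days before baseline = max(0, W − 49 − L):

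| Lag L | W = 59 | W = 62 |
|---|---|---|
| 0 days | 10 | 13 |
| 5 days | 5 | 8 |
| 10 days | 0 | 3 |

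An on-time follow-up answer therefore always includes at least 10 days before app use. Overlap with the baseline window is certain under Reading A. Under Reading B it shrinks with the lag and reaches zero only when a 10-day lag meets a 59-day window.

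**Rough size in people.** The documents give no event rates. As an assumption, let 5% to 20% report an emergency visit in 2 months, with visits spread evenly. With a 61-day window and 12 overlapping days, 12/61 × 5% = 1% and 12/61 × 20% = 4%. In a group of 25 that is about 0.25 to 1 person. Support-service use may be more common, but there is no figure for it.

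**Check of the remedy.** With a 49-day recall and follow-up 49 days after the coaching call, days before app use = 49 − 49 = 0 and days before baseline = 0. If follow-up is instead timed from baseline, a 49-day recall still leaves up to 10 days before app use.

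**The case against.** The other side has several good points.

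- **Nothing is literally counted twice.** A reader might infer that events are double-counted. The affected items ask whether an event occurred, so the most that happens is one event giving a yes on both occasions.
- **Overlap with baseline is not certain.** If the 7 weeks run from the coaching call, a 10-day lag leaves only 0 to 3 days, and a late survey shrinks that further. The time before app use remains under either reading when the survey is on time.
- **Use at baseline is inferred.** The article says that several measures are given at both times but does not say so for this one, and the enrolment list in Recruitment Procedure does not name it. The inference is reasonable, but it is an inference.
- **Little rests on the measure.** It is not a feasibility criterion, it is not among the measures named for effect and variance estimates (PHQ-4 and PROMIS anxiety and depression), and it is not in the planned correlations. The Limitations section already concedes that change cannot be attributed to the apps.
- **A careless remedy would do harm.** By the end of June 2018, 17 + 7 = 24 people had consented against a target of 50. For them, counting only events after baseline (49 days) against a 61-day baseline window makes the baseline window 61/49 − 1 = 24% longer and suggests a fall in use. That is an error in the favourable direction, whereas the present flaw errs towards no change.

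A reader might also infer that paired *t* tests will be applied to these yes/no items. The Data Analysis section says only that changes will primarily be analysed that way and does not assign the test to them. How they are summarised can be left to an analysis plan, so that is not part of the point.

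These arguments limit the scope and shape the remedy. They do not remove the mismatch between a recall of 59 to 62 days and an interval of 49.

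**Conclusion.** The point stands as a minor flaw in a secondary measure. On an on-time follow-up, 10 to 23 days of the window precede app use if the 7 weeks run from baseline, and 10 to 13 days if they run from the coaching call. The part before baseline is 10 to 13 days in the first case and 0 to 13 in the second.

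The expected effect is to pull the pre-post change towards none. That rests on the measure being given at both times and on participants answering the recall period as worded. The likely effect is around one person or fewer per group of 25 for emergency visits under the assumed rates above.

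The finding covers emergency visits and support-service use only. The missed-appointment item and the caregiver primary-care item state no recall period of their own.

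**What to change.** **New participants.** Ask about the past 7 weeks at both time points, and time the follow-up survey 7 weeks after the coaching call. The two windows are then equal, do not overlap, and the later one covers only time with the apps.

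**Participants already enrolled.** Keep the 2-month items. Add a follow-up item asking whether any event has occurred since the date of baseline or of the coaching call, with that date inserted by Qualtrics. Report the resulting proportion descriptively. Do not set it against the longer 2-month baseline window as a change unless the windows are equalised.

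**Cost.** Survey wording, one added item and a stated anchor for the follow-up date. The drawback is two recall wordings in a small sample, so any change estimate should come from participants with equal windows or be labelled accordingly.
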